#### Construction of the network

The template of the neuroimaging research laboratory of Stanford University (Functional Imaging in Neuropsychiatric Disorders Lab website; http://findlab.stanford.edu/functional_ROIs.html) will be used to explore the DMN and SN (54). For the ROIs of the DMN and SN, see Supplementary Tables S1, S2.

We will use the Brain Connectivity Toolbox to extract the connection information between various brain regions and draw the connection diagram at the macro level. This will be used to quantitatively describe the structure, function, connection model and topological characteristics of the human brain network. We will mainly focus on the brain regions related to PUs: the insula, ACC, supplementary motor area (SMA) and prefrontal cortex. We will take the DMN and SN as the main brain function networks to consider.

Degree, global efficiency, local efficiency, path lengths and cluster coefficients will be used to investigate the relationships between the changes in these two brain functional networks and the improvements in tics and PUs and to clarify the possible brain mechanisms underlying the effects of MHRT from the perspective of brain functional networks. We will assess global network integration, segregation and connectivity between modules using the following measures for the DMN and SN: (1) degree: number of edges connected to a node; (2) global efficiency: global transmission capacity of the network; (3) cluster coefficient: degree of network collectivization; (4) local efficiency: nodal connections to within-network nodes; (5) path length: optimal path from one node to another. To assess the reliability of the results and enhance comparability with previous research, exploratory analyses on the absolute Fisher r-to-z transformed Pearson correlation connectivity matrices will be performed using the same graph indices. The calculation formulas for these parameters are presented in Supplementary Figure S2.

### Statistical analysis

Measures will be analyzed using IBM SPSS Statistics version 22 (IBM, Armonk, NY, United States).

First, the efficacy of MHRT will be tested using repeated measures analysis of variance (ANOVA). A 3 × 3 mixed design will be used to examine the main effects of group (MHRT, HRT or PST) as a between-subjects factor and time point as a within-subjects factor, as well as interaction effects. Second, for the imaging study, we will assess connectivity between the DMN and SN and compute the average Fisher r-to-z transformed Pearson correlations of the resting-state fMRI time-series between the nodes that belong to these resting-state networks. Pearson correlations will be used to replicate earlier functional connectivity studies. For analysis of the abovementioned neuroimaging indices, we will use univariate mixed-model analyses to assess the effects of MHRT and HRT. We will use the after-training outcomes as dependent variables, the group (MHRT, HRT, PST, and HC) as the independent variable and the baseline measure of the outcome as a covariate. We will also perform these analyses correcting for age, years of education and sex.

Measurement data will be presented as the mean ± standard deviation (x ± s). The demographic and efficacy indices of the three intervention groups before and after the intervention will be compared by multifactor analysis of variance (measurement data), and repeated measures analysis of variance and paired *t*-tests will be used for comparisons between multiple groups and before and after the intervention. In addition, we regarded at least 30% changes in YGTSS scores $\left[(\frac{\mathrm{Pr}e_{\left(YGTSS\right)}-Post_{\left(YGTSS\right)}}{\mathrm{Pr}e_{\left(YGTSS\right)}}\right)\times 100\%]$ as the clinically meaningful level.

For the analysis of global graph measures, we consider a significance level of α = 0.05 significant. To correct for multiple comparisons in subnetwork analyses, we will use a D/AP-Sidak adjustment that considers the mutual correlation between outcome measures (https://www.quantitativeskills.com/sisa/calculations/bonhlp.htm). For between-network connectivity analyses, we will compute an α corrected for three comparisons, i.e., adjusted for the correlation (*r* = 0.544) between the three indices after training (αBN = 0.031). For subnetwork graph analyses, we will compute a separate α for each graph measure adjusted for the correlation between the respective subnetwork measures at baseline (rFPN = 0.387, αFPN = 0.026; rDMN = 0.408, αDMN = 0.026; rSN = 0.413, αSN = 0.027).

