#### Sample size estimation

In accordance with the experimental design, three groups of participants will be included: the HRT group, MHRT group, and psychological education and supportive therapy (PST) group.

In addition, for the sample size, we use the formulas (see Supplementary Figure S1) to **calculate** the sample size (α = 0.05, 1–β = 0.8). Taking YGTSS scores as the indicator of a curative effect and based on the effect size of 0.68 calculated in a preliminary pilot test, it was calculated that at least 23 participants were needed in each group, and the drop-out rate was estimated to be 20%. Based on previous experience, 15% of MRI scans have invalid data, resulting in at least 34 subjects being required in each group (38). Therefore, 40 patients will be recruited in each group, for a total of 120 patients in this study. In addition, another 40 healthy controls will be recruited as blank controls for the behavioral and imaging research. A total of 160 participants will be included.

All evaluators will be blinded, and the treatment condition assignment will not be disclosed until after the intervention. The clinical evaluator will not be informed of which therapeutic modality the participants will receive in the evaluation process. Moreover, all dropouts must be accounted for and reported. The reasons for dropouts are mentioned. Intention-to-treat analysis was used to assess the missing data.

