## Limitations

The symptoms of tic disorder are characterized by volatility. Its severity will be affected by life events, emotions, physical diseases such as infection and so on. Such fluctuations will affect our judgment of the treatment effect. To reduce misjudgment, we will use a scale related to life events and emotions in the evaluation and establish a 3-month follow-up period.

To ensure the quality of and effects obtained with this RCT, we will adopt a one-on-one treatment protocol. Due to the lack of therapists, our experiment will take a long time. In this process, participants will be required to come to the clinic at a fixed time every week. This may also result in the loss of these school-age participants. Online training and group therapy may be ways to solve this problem in the future.

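### Intention-to-treat is named as the handling of missing data, but the repeated-measures ANOVA, run as written, analyses completers only: up to about 24 of 120 randomised children lost at the planned 20% drop-out

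*Protocol article*

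**What the plan says.** All references are to the protocol article.

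- **Efficacy test (Statistical analysis).** "First, the efficacy of MHRT will be tested using repeated measures analysis of variance (ANOVA"). The layout follows: "A 3 × 3 mixed design will be used to examine the main effects of group (MHRT, HRT or PST) as a between-subjects factor", with time point as the within-subject factor. The three time points are not named. Paired t-tests are added for before-after comparisons.
- **Software (Statistical analysis).** "Measures will be analyzed using IBM SPSS Statistics version 22".
- **Missing data (Sample size estimation).** The one sentence on method is "Intention-to-treat analysis was used to assess the missing data". The same paragraph requires drop-outs to be reported with reasons.
- **Expected loss (Sample size estimation).** "the drop-out rate was estimated to be 20" per cent, and the group size is inflated for it. Limitations adds that families must attend weekly at a fixed time: "This may also result in the loss of these school-age participants".
- **Visits (Assessment procedures).** Baseline, inside a week of the eighth session, one month later, and follow-up at three and six months.
- **Mixed models (Statistical analysis).** Named for the neuroimaging indices only. No imputation, carry-forward or likelihood-based method is named for the clinical outcomes.

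**The concern.** The article makes two positive statements that do not fit together as they stand. One offers intention-to-treat as the way missing values are dealt with. The other fixes an analysis that, in the named software, removes listwise every child with a gap at a modelled time point. A paired t-test likewise needs both values.

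Three things are at stake. First, a completers' result could be published as an intention-to-treat result for the main efficacy comparison. Second, completers are selected after randomisation, so the comparison no longer has the full protection of the random allocation. Third, data are wasted: a child assessed after session 8 who misses a later modelled visit contributes nothing, although the post-training score is the one closest to the primary outcome in the Abstract (change from baseline to the end of training).

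If the missing-data method is chosen only after the data are seen, the choice can also be suspected of being driven by the result.

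**Working it through.** **1. The plan's own inflation.** Inputs from Sample size estimation: 23 per group, 20% drop-out, 15% invalid MRI.

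23 / (1 − 0.20) / (1 − 0.15) = 23 / 0.80 / 0.85 = 33.8, so 34.

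This reproduces the stated figure ("15% of MRI scans have invalid data, resulting in at least 34 subjects being required in each group"). Dividing by the retained share treats drop-outs as absent from the analysis, which agrees with a completers' analysis and not with one that keeps everyone. (The base of 23 comes from a formula in a supplementary figure that is not shown. It is not checked here and nothing below depends on it.)

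**2. Children left in the ANOVA.** 40 randomised per arm, 120 in all.

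- Complete cases per arm: 40 × 0.80 = 32.
- Total: 3 × 32 = 96.
- Lost: 120 − 96 = 24, or 8 per arm.

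This assumes that the whole 20% has a gap within the three modelled visits. The article does not say by which visit the 20% accrues.

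**3. Intermittent gaps (assumption).** If 5% to 10% of the remaining children also miss each of the two post-baseline modelled visits:

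- 5%: 40 × 0.80 × 0.95² = 28.9, about 29 per arm.
- 10%: 40 × 0.80 × 0.90² = 25.9, about 26 per arm.

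**4. Illustrative precision cost.** The plan gives "α = 0.05, 1–β = 0.8" and an effect size of 0.68 without stating its type. Reading it as a standardised mean difference between two arms, with a two-sided test (both assumptions), normal-approximation power is 0.86 with 40 per arm and 0.78 with 32. The 0.86 is an upper bound for any method that keeps all children, because missing values still cost information.

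**5. Can bias be sized?** Only under invented correlations and drop-out mechanisms. Two sets of simulations, both with about 20% drop-out occurring after the post-training visit:

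| Assumed set-up | Completers' result |
|---|---|
| No true effect; visit correlations 0.5/0.8/0.5; drop-out random in one arm, driven by the post-training score in the other | Spurious difference of 0.06 to 0.09 SD in change to the last visit |
| True difference 0.68; first-order autoregressive correlation 0.6 or 0.8; same score-driven rule in both arms | 0.63 to 0.68 at the post-training visit; 0.68 at the last visit |

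One set-up creates a difference where there is none; the other leaves the true difference alone or shrinks it slightly. Size and direction follow the assumptions, so these figures are illustrations only.

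**6. Who is lost, and when.** The first post-baseline assessment comes only after session 8. A child who leaves during the weekly sessions, the route described under Limitations, will normally have a baseline YGTSS and nothing else. A mixed model that takes baseline as a covariate and requires a post-baseline score would exclude the same child as the ANOVA. The remedy must allow for this.

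**The case against.** The strongest reply is that the two statements can coexist. If values are imputed before the ANOVA, all randomised children enter it. A journal article may leave the imputation technique to a fuller document that is not shown. A reader might infer that the statements are irreconcilable; the documents do not support that. What stands against the reply is that the article is not merely silent. It gives intention-to-treat as the answer to missing data, which it cannot be, and pairs it with a test that deletes incomplete cases. Nor does the phrase mixed design help: here it means a between- and within-subject ANOVA, not a mixed model.

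Other points on that side are sound:

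- **Counts.** A reader might infer that any missed visit removes a child, and that losses grow over all five visits. The design has three time points, and missing only a visit outside the model removes nobody. The figure of 24 is therefore conditional.
- **Differential drop-out.** A reader might infer that drop-out will depend on arm or response. That is possible, but no document shows it. All arms have eight sessions on a common time frame, so the burden of attendance is shared.
- **Bias.** A reader might take 0.06 to 0.09 SD as the expected error, 8% to 13% of 0.68. It comes from one deliberately one-sided set-up.
- **Allowance for loss.** The plan recruits 40 against 34 required, and 32 completers still exceed its base of 23. This protects numbers, but does not make the analysis intention-to-treat.
- **Choice of remedy.** Multiple imputation before the planned ANOVA would also resolve the conflict, so a mixed model is not the only acceptable answer.

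**Conclusion.** The point holds in this form: as written, with no imputation step, the efficacy test is a completers' analysis described as intention-to-treat. It rests on the listwise deletion of repeated-measures ANOVA in SPSS and on the absence from the article of any method that supplies or models missing clinical scores.

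Size: up to about 24 of 120 randomised children (8 per arm) outside the efficacy comparison at the planned 20% drop-out, if all of it falls within the modelled visits; fewer if some falls at visits outside the model, more if intermittent gaps are added. Power of 0.86 against 0.78 is indicative and depends on how 0.68 is read. No material bias is demonstrated, and the documents do not allow its size or direction to be derived.

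This should be fixed, because the main comparison is affected and the remedy is cheap. The evidence does not support calling the trial's result invalid without it.

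**What to change.** 1. **Model.** Replace the repeated-measures ANOVA for YGTSS by a likelihood-based mixed model for repeated measures (MIXED in the same SPSS) on all randomised children, in the arm to which they were randomised. Include arm, visit and arm-by-visit, with unstructured covariance. Enter baseline YGTSS as one of the repeated outcomes, with a common baseline mean across arms, so that a child with only a baseline value stays in the model. Name the visits.
2. **Alternative.** Keep the planned ANOVA and state that multiple imputation precedes it, with the imputation model described.
3. **Sensitivity analysis.** Add a delta-adjusted or reference-based analysis. It matters most for children with no post-baseline score: keeping them in the model adds no information on their outcome, and the main analysis rests on data missing at random.
4. **Wording.** Keep the intention-to-treat commitment, but reword the sentence under Sample size estimation so that it defines the analysis population. State the missing-data method separately under Statistical analysis.

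Cost: revised wording and a little more programming, including the constraint on the baseline means. No new software, visits or participants. Settle it before treatment assignments are disclosed.

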**Methods/design:**

We will perform a randomized control trial (RCT) to evaluate the efficacy and neural mechanisms of MHRT. The sample will include 160 participants (including 120 patients with TS and 40 healthy controls). The patient sample will be randomly divided into three groups exposed to three different types of training: MHRT, HRT, and psychoeducation and supportive therapy (PST). Participants will be assessed and undergo resting-state fMRI scans at baseline and at the end of the 12-week training. The Yale Global Tic Severity Scale (YGTSS) and Premonitory Urge for Tic Scale (PUTS) will be used to assess the severity of tic symptoms and premonitory urges. The primary outcomes are change scores on the YGTSS and other assessments from baseline and the end of the training. The secondary outcomes are the neural correlates of these trainings among these groups based on graph theory, which is used to characterize brain functional connectivity networks. The default mode network (DMN) and the salience network (SN) will be assessed (which have been associated with mindfulness as well as the generation of tic symptoms) by network parameters, including clustering coefficients and shortest path lengths. Changes in these network parameters will be regarded as the neural correlates of the behavioral training.

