### Assessment procedures

The clinical evaluation process will mainly be completed by two attending child psychiatrists. Before the formal evaluation, an evaluation of the consistency between raters will be completed. The clinical evaluation will be carried out only after the consistency of the raters is above 0.85. The time points for the evaluation mainly included the baseline test, within 1 week after the completion of eight sessions of intervention, and at the end of 1 month after eight sessions of intervention. The patients will be followed up at the end of 3 and 6 months after the eight sessions of intervention. For more details, see Figure 1.

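### The YGTSS efficacy analysis makes no covariate use of baseline, although the imaging analysis does; the test is valid but gives up power, by an amount that depends on quantities the protocol does not state

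*Protocol article*

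**What the plan says.** The Abstract (Methods/design) sets the endpoint: "The primary outcomes are change scores on the YGTSS and other assessments from baseline and the end of the training". The Statistical analysis section sets the efficacy model: "A 3 × 3 mixed design will be used to examine the main effects of group (MHRT, HRT or PST) as a between-subjects factor", with time point within subjects and the interaction also examined. It does not name the three time points. Assessment procedures begins its list as follows: "The time points for the evaluation mainly included the baseline test, within 1 week after the completion of eight sessions of intervention". The list then adds a visit one month after the sessions, and 3 and 6 months are described separately as follow-up. Baseline, end of training and one month are therefore the natural three levels.

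The other clinical tests named are multifactor ANOVA, repeated-measures ANOVA and paired t-tests, and none carries a baseline covariate. Baseline YGTSS is otherwise used as the denominator of the 30% response criterion.

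For the imaging indices, the same section regresses the after-training value on group with "the baseline measure of the outcome as a covariate". The adjustment for age, education and sex follows that imaging sentence.

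Sample size estimation uses YGTSS ("Taking YGTSS scores as the indicator of a curative effect"), with "α = 0.05, 1–β = 0.8" and a required size "based on the effect size of 0.68 calculated in a preliminary pilot test".

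**The concern.** The trial was sized on YGTSS, yet YGTSS gets the less efficient model and the secondary imaging indices get the more efficient one. No reason is given.

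Two features of the stated clinical model matter. First, a change score or group-by-time contrast subtracts baseline with a fixed slope of 1. When rho is below 1 (equal variances at the two visits), that slope is too steep. Residual variance is then larger than it need be, and a chance baseline difference between arms is over-corrected. Second, the model lists a main effect of group. If baseline is one of the levels, this effect averages in a visit at which randomised arms have no expected difference.

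At stake is the chance of detecting a real benefit of MHRT. The contrast with HRT is between two active arms, so it may well be the smaller one, and power is least easily spared there.

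**Working it through.** **The plan's own figure.** The protocol states that "at least 23 participants were needed in each group". A standard two-sample t-test with effect 0.68, two-sided alpha 0.05 and 80% power needs 35 per group (one-sided 28), so 23 is not reproduced by that route. The formula is in a supplementary figure that is not shown, so this counts neither for nor against the point. The inflation step does reproduce: 23 / (0.80 × 0.85) = 33.8, so 34.

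**Inputs.** From the documents: effect 0.68, alpha 0.05, and 40 per arm less 20% drop-out = 32 per arm. Assumed: two-sided testing, equal variances at the two visits, and rho between 0.3 and 0.8. The documents give no rho and do not say which SD scales the 0.68, so both scales are shown.

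**Formulas.** In units of the single-visit variance, the change score has variance 2(1−rho) and the baseline-adjusted comparison has residual variance 1−rho². Their ratio is (1−rho²) / [2(1−rho)] = (1+rho)/2, which is below 1 whenever rho is below 1.

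- If 0.68 is in change-SD units: change effect 0.68; adjusted effect 0.68/√((1+rho)/2).
- If 0.68 is in post-score SD units: change effect 0.68/√(2(1−rho)); adjusted effect 0.68/√(1−rho²).

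Example at rho = 0.5: the variance ratio is 0.75 and the adjusted effect is 0.68/√0.75 = 0.785 on either scale.

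**Two arms, one post-training visit, 32 per arm** (noncentral t, one degree of freedom fewer for the adjusted model):

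| rho | Change-SD: change → adjusted | Gain (points) | Post-SD: change → adjusted | Gain (points) |
|---|---|---|---|---|
| 0.3 | 76.4% → 91.3% | 15 | 61.9% → 80.1% | 18 |
| 0.5 | 76.4% → 87.1% | 11 | 76.4% → 87.1% | 11 |
| 0.7 | 76.4% → 82.7% | 6 | 93.3% → 96.3% | 3 |
| 0.8 | 76.4% → 80.6% | 4 | 98.8% → 99.4% | under 1 |

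With 40 per arm and rho = 0.5, power goes from 85.2% to 93.4%.

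**Group main effect over baseline and two post visits** (post-score SD units, equal correlations between visits, constant effect after baseline). The effect averages to (0 + 0.68 + 0.68)/3 = 0.453, which is two thirds of 0.68. The SD of the three-visit mean is √((1+2rho)/3), or 0.816 at rho = 0.5. The standardised effect is 0.453/0.816 = 0.555. Power at 32 per arm is 59% at rho 0.5 and 48% at rho 0.8. This weakness grows with rho, while the loss from change scores shrinks.

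**The 3 × 3 interaction itself.** This was simulated with 32 per arm, equal correlations, and one arm better by 0.68 post-score SD at both post visits. Power was 67% at rho 0.3, 83% at 0.5 and 97.4% at 0.7. A three-arm baseline-adjusted test at one post visit had 83%, 89% and 97.9%. The direction is the same as in the table; the gap closes as rho rises.

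**The case against.** The strongest reply is that nothing here is invalid. Under randomisation the change comparison and the group-by-time contrast are unbiased, and with 40 per arm at rho = 0.5 the change-score power of 85% is already above the planned 80%. That stands: this is lost efficiency, not bias, and a reader who infers that the planned test is wrong goes beyond the documents.

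A reader might also infer a fixed loss, say 6 to 11 points. The documents do not support one. That band needs rho of 0.5 to 0.7, 32 per arm and 0.68 in change-SD units, and it describes a two-arm, single-visit contrast, not the planned 3 × 3 test.

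A third tempting reading is that efficacy will be judged on the group main effect. The section lists main effects and the interaction together and singles out neither; a change-score endpoint corresponds to the interaction. The 59% is therefore a warning about one listed effect, not the power of the trial.

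It can also be said that the imaging model is an imperfect benchmark, because scans occur only twice and that model includes non-randomised healthy controls. It is also true that the three time points are inferred, and that no calculation is available for an MHRT–HRT effect smaller than 0.68. All this is fair, but none of it explains why a baseline the trial already collects is left out as a covariate for YGTSS. Nor is this a detail left to an unseen analysis plan: the article names the model, its factors and its effects.

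**Conclusion.** The point holds as one of efficiency and internal consistency. The direction needs no outside figure: with equal variances, baseline adjustment has the smaller error variance for every rho below 1, at the price of one degree of freedom.

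The size cannot be fixed from the documents. Over rho 0.3 to 0.8 and both scales of the 0.68, the gain runs from under 1 to about 18 points for two arms of 32 at one visit. It is substantial at low to moderate correlation. It becomes negligible at high correlation if 0.68 is in post-score SD units. The dilution of the group main effect to two thirds rests on baseline being one of the three levels and on a constant effect after baseline. The change is worth making because it is almost free.

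**What to change.** In the Statistical analysis section, make the primary YGTSS test a model of post-baseline YGTSS on randomised group (MHRT, HRT, PST) with baseline YGTSS as a covariate. This is the form already stated for imaging, without the healthy-control level. If more than one visit is modelled, put only post-baseline visits in the time factor and keep baseline as a covariate. State that a group main effect averaging over baseline will not be taken as evidence of efficacy. Keep change scores as descriptive summaries.

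The cost is one degree of freedom and a few lines of wording. No extra patients, visits or data are needed.

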**Discussion:**

MHRT was newly developed for the treatment of TS. MHRT may lead to greater reductions in tic severity than traditional HRT. Changes in the network parameters of the DMN and SN may show associations with the efficacy of MHRT.

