## Discussion

This protocol describes a study assessing the efficacy of MHRT for children with TS and associated brain network mechanisms. To the best of our knowledge, this is an original intervention technology that may be valuable for the non-drug treatment of TS. The protocol was designed to investigate multiple aspects of the treatment response, not only tic severity but also the effects of MHRT, HRT and PST on psychosocial functioning and neural physiological mechanisms.

Our results may be consistent with previous studies in patients with TS that compared the effectiveness of HRT and PST in a similarly large sample of TS patients. Based on available pilot data, we predict that patients receiving MHRT or HRT may show significant and clinically meaningful reductions in tic severity compared with patients receiving PST. We speculate that augmenting HRT with mindfulness training will enhance tic severity reductions and result in stronger awareness and lower anxiety levels. The fMRI scans may show functional changes in brain networks associated with mindfulness.

Mindfulness training can improve performance in attention, working memory and cognitive control tasks (55–57). With the potential benefits of mindfulness in children with common neurodevelopmental disorders (58), more research has been conducted in recent years. In 2020, a study investigated the feasibility of a family-based mindfulness intervention in 100 attention-deficit/hyperactivity disorder (ADHD) children's families and found that the intervention group showed greater improvements in children's ADHD symptoms (59). In 2021, Muratori et al. in a 50-child sample of adolescents with ADHD and oppositional defiant disorders showed that participating in a mindfulness meditation was associated with a greater reduction in hyperactive behaviors in the school context (60). Another pilot study using mindfulness training for children aged 8–12 years with ADHD (*n* = 140) and their parents also showed promising results (61). A study in Hong Kong demonstrated the feasibility of a mindfulness program in the Chinese context (62). Accumulating evidence supports the applicability of mindfulness-based therapy for those with mental health and neurodevelopmental disorders. The theoretical basis suggests that it can also be beneficial for patients with TS.

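### The stated test of MHRT's efficacy is an omnibus three-arm ANOVA with no named MHRT-HRT contrast, so it cannot by itself support the hypothesis that MHRT beats HRT

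*Protocol article*

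**What the plan says.** The Abstract's closing Discussion paragraph gives the added value expected of the new therapy: "MHRT may lead to greater reductions in tic severity than traditional HRT". The main Discussion repeats it ("We speculate that augmenting HRT with mindfulness training will enhance tic severity reductions") beside a second prediction, attributed to pilot data, that "patients receiving MHRT or HRT may show significant and clinically meaningful reductions in tic severity compared with patients receiving PST".

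Under Statistical analysis the clinical test is stated affirmatively: "the efficacy of MHRT will be tested using repeated measures analysis of variance (ANOVA"). The next sentence gives its form: "A 3 × 3 mixed design will be used to examine the main effects of group (MHRT, HRT or PST) as a between-subjects factor", with time point as the within-subjects factor and the interaction also examined. The following paragraph adds that "repeated measures analysis of variance and paired *t*-tests will be used for comparisons between multiple groups and before and after the intervention".

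No MHRT-HRT contrast is named for the YGTSS, and no ANOVA term is named as the deciding one. For imaging, the same section uses a different model: the post-training value as outcome, group as factor and the baseline value as covariate. The multiplicity adjustment that follows concerns imaging only.

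**The concern.** The hypothesis that justifies adding mindfulness to HRT is a difference between two particular arms. The procedure assigned to it asks whether three arms differ in any way, and whether an arm changes over time. Each of those can be significant when mindfulness adds nothing.

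This case is realistic. The protocol itself expects HRT to beat PST. If it does, and MHRT merely matches HRT, the omnibus test is likely to be significant. A result reported under the label of MHRT efficacy could then be taken as support for MHRT over HRT without evidence for it.

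**Working it through.** **Inputs.** Arms of 40 with 20% drop-out (Sample size estimation): 40 × 0.80 = 32 per arm. Effect size δ = 0.68 (same section); the text does not say what it compares, so it is taken here as a between-arm difference in SD units, present at every post-baseline visit. Three arms and three visits (Statistical analysis). α = 0.05, assumed two-sided. The correlation ρ between visits is not given; 0.5, 0.6 and 0.7 are assumed, equal for all pairs of visits, with unit SD.

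**The plan's own figure.** None is given for the behaviour of this ANOVA. The nearest is the sample size: 23/(0.80 × 0.85) = 33.8, so 34, which reproduces the stated inflation. The 23 itself cannot be checked because its formula is in a supplement not shown. Nothing below depends on it.

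**Group-by-time interaction, F(4, 186).** Arm effects are (δ, δ, 0) when MHRT = HRT > PST, and (δ, 0, 0) when only MHRT works. In both cases the squared deviations from the mean sum to (2/3)δ². The visit profile (0, 1, 1) has squared deviations summing to 2/3. The noncentrality is therefore the same in both cases:

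λ = n·δ²·(2/3)·(2/3)/(1−ρ) = 32 × 0.4624 × 0.4444/(1−ρ) = 6.58/(1−ρ)

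**Group main effect, F(2, 93).** Averaging over baseline shrinks each arm effect to (2/3)δ:

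λ = 3n·δ²·(2/3)·(4/9)/(1+2ρ) = 13.15/(1+2ρ)

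**Paired t-test within one arm** that improves by δ: noncentrality δ√n/√(2(1−ρ)).

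**Direct MHRT-HRT comparison at one visit.** Change score: δ/√(2(1−ρ)·2/n). ANCOVA: δ/√((1−ρ²)·2/n).

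| Probability of p < 0.05, 32 per arm | ρ = 0.5 | ρ = 0.6 | ρ = 0.7 |
|---|---|---|---|
| Interaction, MHRT = HRT > PST | 83% | 91% | 97% |
| Interaction, only MHRT works | 83% | 91% | 97% |
| Group main effect, only MHRT works | 61% | 57% | 53% |
| Paired t-test in MHRT, all arms improve equally | 96% | 99% | >99% |
| MHRT-HRT change-score test, only MHRT works | 76% | 85% | 93% |
| MHRT-HRT ANCOVA, only MHRT works | 87% | 92% | 96% |
| MHRT-HRT ANCOVA, MHRT = HRT > PST | 5% | 5% | 5% |

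Simulating the same settings agreed with these values to within about one percentage point.

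The first two rows are the point. The interaction rejects equally often whether mindfulness adds nothing to HRT or supplies the whole effect. When all three arms improve equally, the interaction correctly stays at about 5%, while the time effect is significant in practically every trial and the paired test in over 95%.

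**The case against.** The strongest reply is that an omnibus test followed by pairwise comparisons is a sound structure, and that a condensed article may leave the pairwise step to the full protocol or analysis plan. Much of this stands. The interaction is a valid test of equal change across arms. Its 83% to 97% rejection rate when PST differs is correct detection of a real difference, not a false-positive rate. An MHRT-HRT change-score test run only after a significant interaction still gives a false MHRT-HRT claim in about 5% of trials when MHRT = HRT > PST, and in about 1.5% when all arms are equal. The interaction also bears on the prediction against PST, which is one of the trial's own hypotheses.

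Three stronger readings are therefore tempting but unsupported.

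- A reader might infer that the plan tests none of its hypotheses. The prediction that MHRT or HRT beats PST rules that out.
- A reader might infer that the planned ANOVA wastes power in general. Only the group main effect does. The interaction has 83% to 97% power when MHRT alone is better, close to ANCOVA, and the text never names the main effect as the deciding term.
- A reader might infer that within-arm paired tests will be offered as proof of superiority. The text says only that ANOVA and paired tests "will be used for comparisons between multiple groups and before and after the intervention", which can be read as ANOVA between groups and paired tests before and after.

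Using different models for imaging and clinical data is likewise not a contradiction. Change-score and baseline-adjusted analyses are both valid in a randomised trial, and the second is usually more efficient.

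The reply does not remove the point. The article does more than leave out a follow-up step: it assigns the efficacy of MHRT to the omnibus procedure.

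**Conclusion.** The concern holds in this form: the clinical efficacy test as written cannot separate MHRT > HRT from no added benefit of mindfulness. At 32 per arm and 0.68 SD, the interaction is significant in about 83% to 97% of trials under either state. The group main effect is the weakest term for this purpose (about 53% to 61% power when MHRT alone is better). A within-arm paired test cannot distinguish treatment from the natural fluctuation of tics that the Limitations section acknowledges.

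The sizes rest on assumed equal visit correlations of 0.5 to 0.7, an equal effect at both post-baseline visits, and 0.68 read as a between-arm difference. At ρ = 0.3 the same formulas give 67% for the interaction (λ = 9.39) in both scenarios. The equality of the two scenarios does not depend on ρ, because their noncentralities are identical.

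**What to change.** Amend the Statistical analysis section before the data are analysed:

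- Analyse the YGTSS with a baseline-adjusted model: ANCOVA, or a mixed model with baseline YGTSS as covariate, as is already planned for imaging.
- Prespecify MHRT minus HRT at one named post-treatment visit as the deciding contrast, with estimate and 95% confidence interval. The Abstract's definition of the primary outcome points to the end of training. Assessment procedures lists four post-treatment assessments, and the ANOVA uses three unnamed time points including any baseline, so the visit needs naming.
- Test MHRT-PST and HRT-PST in a stated order or with a stated alpha.
- Keep the interaction as a supportive joint test. Report the group main effect and within-arm paired t-tests as descriptive only.

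The cost is small: analysis wording, no new data and no extra patients. The sponsor gives up only the option of claiming MHRT efficacy from the omnibus result alone. The direct contrast holds about 5% error and, under the assumptions above, has 87% to 96% power by ANCOVA. If the gain over HRT were half as large (0.34 SD, an assumption), an unadjusted comparison of 32 per arm would have about 27% power. The amended text should therefore also say which two conditions the 0.68 compares.
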